**Fig. 2 f0010:**
[figure not shown]
Possible patterns of recurrence that will be evaluated in exploratory analyses. (A) If the urine test fails to detect many recurrences, there will be a substantial step-up at the 12- and 24-mo cystoscopy time points. (B) If the urine test is similar to cystoscopy, the curves will have similar shapes. (C) If the urine test is better than cystoscopy, there will be a substantial step-up at the 6- and 18-mo urine testing time points.

### Reporting of adverse events

3.3

Adverse events (AEs) will be tabulated for the safety population as proportions with binomial 95% confidence intervals according to the type of surveillance performed as follows: The denominator will be the number of surveillance visits using the Xpert Bladder Cancer Monitor test, the EpiCheck urine test, or cystoscopy. The numerator will be the number of surveillance visits that resulted in a specific AE (eg, gross hematuria, urinary tract infection, etc.) for each type of surveillance performed. Each specific AE will be counted only once per visit. We will report these proportions without formal significance testing, because we anticipate that AEs will be rare and to avoid type 1 errors due to multiple testing.

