### Overview

2.1

This is a phase 2 healthcare delivery parallel trial in which participants will be randomized 1:1:1 to programmatic surveillance with the Xpert Bladder Cancer Monitor or the EpiCheck urine test versus frequent cystoscopy at 6, 12, 18, and 24 mo (see the study schema in Fig. 1). Frequent cystoscopy is the standard of care according to current guideline recommendations [1], [16]. In the urine testing arms, urine testing will replace cystoscopy at the 6- and 18-mo marks.

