### Objective and outcomes

2.3

The primary objective is to determine whether urinary quality of life during surveillance is improved in the urine testing arms. We chose the primary outcome, patient-reported urinary quality life, based on (1) importance of the outcome to patients (Table 2) and (2) feasibility and rationale for evaluation in a phase 2 clinical trial. Oncological outcomes (eg, progression of disease) and complications were ranked highest by patients. However, progression and complications are rare and would require a very large study for adequate power. Discomfort was ranked third, and we considered this as the primary outcome. However, we felt that discomfort was too closely linked to the number of cystoscopy procedures that patients undergo in each arm. As such, this would clearly favor the urine testing arms, where patients undergo only two procedures instead of four scheduled procedures over the 2-yr study period (see the study schema in Fig. 1). For these reasons, oncological outcomes, complications, and discomfort were included as exploratory outcomes. Urinary quality of life 1–3 d after surveillance was ranked fourth and was chosen as the most meaningful and feasible primary outcome. For patients with a positive or nondiagnostic urine test, this outcome will be ascertained 1–3 d after the cystoscopy triggered by the urine test.

**Table 2 t0010:** Outcomes for the Replace Cysto trial

Rank	Outcome	How included in our study
1	Oncological outcomes, ie, not delaying detection of tumors	Exploratory outcome that will be assessed further in subsequent larger comparative effectiveness study if primary outcome is met
2	Complications of surveillance, eg, infections, strictures	Added as an exploratory outcome, not primary due to rarity of these events
3	Discomfort experienced after surveillance testing	Exploratory outcome, not primary as likely directly related to cystoscopy
4	Burden of surveillance, eg, urinary quality of life, anxiety	Primary outcome: urinary quality of life; exploratory outcome: anxiety
5	Number of cystoscopy procedures	Exploratory outcome

Rank indicates importance assigned by patients and caregivers, with “1” being most important. The five most important outcomes are shown out of a total list of nine reviewed with patients. These are previously unpublished data from workshopping the study with bladder cancer patients during the 2021 Bladder Cancer Advocacy Network’s Bladder Cancer Summit.

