#### Quality of life data (primary and exploratory outcomes) and complications (exploratory outcome)

2.6.1

The primary outcome is the patient-reported urinary quality of life domain score of the validated QLQ-NMIBC24 instrument, measured after surveillance. Exploratory outcomes include other QLQ-C30 and QLQ-NMIBC24 domains as well as anxiety and acceptability. These will be obtained by the clinical research coordinator via a phone survey 1–7 d after consent/randomization and after each surveillance visit via the general QLQ-C30 combined with the bladder cancer–specific QLQ-NMIBC24 [20], via the PROMIS Anxiety Scale [21], and via the Acceptability of Intervention Measure [22]. To encourage participation and to offset the burden of completing the quality of life surveys, participants will receive $20 per completed survey as a small token of appreciation for their time, effort, and inconvenience related to study participation.

For the purpose of collecting quality of life assessments, surveillance visits will be defined by the entire surveillance episode, which will include laboratory processing and communication of test results in the urine testing arms and, if applicable, also a cystoscopy triggered by a positive or nondiagnostic urine test.

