We assumed 20% missing data for the primary outcome at each time point. In line with prior work [28], we assume that cancer recurs at a rate of 10%/yr (exponential distribution). Patients see bladder cancer surveillance visits as the highest priority [29]—as such attrition is expected to be low. However, we have conservatively assumed a 10% attrition rate per year.

The simulation is based on the power to show that at least one of the urine test arms is superior to the frequent cystoscopy arm at a Bonferroni corrected 0.025 type 1 error rate, within a mixed-effect model with a random effect for the participant and a structural model with a main effect for the 6-, 12-, 18-, and 24-mo time points and their interaction with the study arm. This is similar to the power of a multivariate Wald test of the equivalence of all three arms at a type 1 error rate of 5%.

Under these assumptions, our study of 240 participants (80 participants per arm) has sufficient power (80%) to detect an effect size of 0.6 standard deviations (green cell in Table 3). This corresponds to a concordance (Mann-Whitney proportion) of 66%. That is, we assume that 66% of the time, a participant who was randomized to a urine testing arm will have a significantly better urinary domain score at 6 or 18 mo than a person who was randomized to the frequent cystoscopy arm.

We acknowledge that the trial is not adequately powered to address some of the exploratory outcomes, for example, complications, bladder cancer recurrence, and bladder cancer progression, given the rarity of these outcomes. Analyses will account for sex as a biological variable using it as a potential covariate in statistical models and subgroup analyses. Given that this is a phase 2 healthcare delivery trial, we will have limited power to determine whether sex modifies the treatment effect. However, if women had zero change in urinary quality of life with urine testing while men would have an improvement of 1.4 standard deviations on the urinary symptom domain scale, we would have 80% power to detect the heterogeneity of treatment effect.

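### Adverse-event intervals treat repeated visits by one participant as independent, and events after a triggered cystoscopy have no assigned row

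*Protocol article*

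**What the plan says.** The Reporting of adverse events section (3.3) fixes four features of the table for the safety population.

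- Interval and rows: events are shown as "proportions with binomial 95% confidence intervals according to the type of surveillance performed".
- Unit: "The denominator will be the number of surveillance visits using the Xpert Bladder Cancer Monitor test, the EpiCheck urine test, or cystoscopy".
- Counting rule: "Each specific AE will be counted only once per visit". A participant with the same event at three visits therefore enters the numerator three times.
- Inference: "We will report these proportions without formal significance testing".

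The visit counts come from the design. In the urine arms "urine testing will replace cystoscopy at the 6- and 18-mo marks" (Overview, 2.1), and in those arms "patients undergo only two procedures instead of four scheduled procedures over the 2-yr study period" (Objective and outcomes, 2.3).

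Two other places bear on the point. Section 2.6.1 says that "surveillance visits will be defined by the entire surveillance episode", including any cystoscopy triggered by the urine result, but it limits this definition to the collection of quality of life data. Exploratory outcome analyses (3.2.4) plans a separate analysis of complications as counts over follow-up time: a mixed-effects Poisson model with a participant random intercept and the fixed effects of the primary model, hence by arm.

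**The concern.** A plain binomial interval assumes independent units. Here the units are repeated visits by the same people, and some participants will be more prone than others to infection or haematuria. The protocol allows for this dependence in the primary model and in the complications model, but not in the adverse-event table.

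The rows raise a second question. A urine visit with a positive or nondiagnostic result leads to a cystoscopy, so one surveillance episode can involve both procedures. Section 3.3 does not say whether an event after that cystoscopy belongs to the urine row, the cystoscopy row or both. Timing does not settle it, because section 2.2 describes the cystoscopy after a positive test as immediate while section 2.6 allows up to 1 month; those two sections should be reconciled. Two analysts could follow section 3.3 and report different urine-row rates.

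At stake are the stated precision and the readability of the safety table in a trial whose purpose is to compare surveillance programmes.

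**Working it through.** The plan states no adverse-event rate, interval width or adverse-event ICC, so there is no figure of its own to reproduce. The ICC of 0.7 in Power calculations (3.1) is for the urinary quality of life score and is not used here.

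**Inputs from the document:** 80 participants per arm; 2 urine visits and 2 cystoscopies per urine-arm participant, 4 cystoscopies per control participant; sensitivity and specificity 72% and 76% (Xpert), 74% and 84% (EpiCheck); recurrence 10% and attrition 10% per year.

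**Assumed:** adverse-event ICC 0.05-0.30; recurrence found at 2.5-5% of urine visits; adverse-event rate 5% per visit where a rate is needed.

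**1. Scheduled visits per row**
- Each urine row: 80 × 2 = 160.
- Cystoscopy row: 80 × 4 + 160 × 2 = 640, of which 320 come from the urine arms.

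**2. Weighted cluster size, m_w = Σm² / Σm**
- Urine row: (80 × 4) / 160 = 2.
- Cystoscopy row: (80 × 16 + 160 × 4) / 640 = 1920 / 640 = 3.

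**3. Standard-error inflation, √[1 + (m_w − 1) × ICC]**

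| Row | ICC 0.05 | ICC 0.10 | ICC 0.30 |
|---|---|---|---|
| Urine (m_w = 2) | √1.05 = 1.02 | √1.10 = 1.05 | √1.30 = 1.14 |
| Cystoscopy (m_w = 3) | √1.10 = 1.05 | √1.20 = 1.10 | √1.60 = 1.26 |

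With the stated recurrence and attrition acting from month 3, about 137 urine visits per test and 508 scheduled cystoscopies are expected. The cluster sizes fall to about 1.9 and 2.8, and the ranges to 1.02-1.13 and 1.04-1.24.

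**4. Practical size.** With 32 events in 640 cystoscopies (5%), the exact binomial interval is 3.4% to 7.0%, a width of 3.5 percentage points. Multiplied by the inflation factor, the width is 3.5 × 1.05 = 3.7 points at ICC 0.05 and 3.5 × 1.26 = 4.4 points at ICC 0.30.

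**5. Coverage.** A beta-binomial simulation (8,000 replicates, 5% rate, no attrition) gave these coverages for nominal 95% exact (Clopper-Pearson) intervals:
- Cystoscopy row: 94.4%, 93.5%, 91.3% and 88.0% at ICC 0.05, 0.10, 0.20 and 0.30.
- Urine row: 97.2%, 96.4%, 96.0% and 94.8% at the same values.

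**6. Urine visits that also lead to a cystoscopy**, recurrence × sensitivity + (1 − recurrence) × (1 − specificity)
- Xpert: 0.025 × 0.72 + 0.975 × 0.24 = 25.2%; 0.05 × 0.72 + 0.95 × 0.24 = 26.4%.
- EpiCheck: 0.025 × 0.74 + 0.975 × 0.16 = 17.5%; 0.05 × 0.74 + 0.95 × 0.16 = 18.9%.

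Nondiagnostic results would add to these.

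**7. What the rows cannot show.** Suppose a 5% event risk per cystoscopy in every arm, none from urine collection, and false-positive triggers only. The cystoscopy row then shows 5% whichever arm the procedures come from. Expected events per participant are 4 × 0.05 = 0.20 with frequent cystoscopy, 2 × 0.05 + 2 × 0.24 × 0.05 = 0.124 with Xpert, and 2 × 0.05 + 2 × 0.16 × 0.05 = 0.116 with EpiCheck.

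**The case against.** The strongest reply is that the table answers a legitimate descriptive question, how often an event follows each kind of procedure, and that pooling cystoscopies across arms suits that question. This stands, and it is why the table should be kept.

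A reader might infer that the trial has no analysis of harm by randomised arm. The document does not support that: section 3.2.4 models complications by arm with a participant random intercept. Nor is it shown that this model will fail. With an assumed 2% event rate per visit and 80 participants, an arm-by-visit cell is empty with probability 0.98^80, about 20%, so its arm-by-visit terms may be unstable if events are sparse. Arm-level rates per person-time would still be obtainable.

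A reader might also infer that the table makes the urine tests look safer. That direction is not established. Counting triggered-cystoscopy events in the cystoscopy row would move them out of the urine rows; applying the episode definition of section 2.6.1 would keep them there. Section 3.3 chooses neither.

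Finally, a reader might apply four visits to everyone and get √(1 + 3 × 0.30) = 1.38. The scheduled cystoscopy row mixes 80 participants with four visits and 160 with two, so 1.26 is the figure at that ICC. An ICC of 0.30 is itself high: at a 5% rate, one event would raise the chance at another visit to 0.05 + 0.30 × 0.95 = 33.5%. No formal test uses the intervals, and the stopping rules in section 3.4 rest on recurrence and progression only.

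**Conclusion.** The point holds, at modest size. The stated intervals ignore within-participant dependence that the protocol models elsewhere. The shortfall is negligible in the urine rows when an exact interval is used. In the cystoscopy row it is small at ICC 0.05-0.10 and becomes material from about 0.20-0.30. All of this rests on assumed ICC values.

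The row ambiguity does not depend on the ICC. It affects roughly a quarter of Xpert visits and a sixth to a fifth of EpiCheck visits, given the stated test characteristics and the assumed recurrence per visit. It is a gap in definition with no known direction of bias.

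**What to change.** - Keep the per-visit table by procedure, but replace the plain binomial intervals with participant-clustered ones (robust/GEE or bootstrap).
- Show urine test plus triggered cystoscopy as its own row, so that each event has one defined place.
- Add a descriptive table by randomised arm: participants with each event, and events per person-time, with events after triggered cystoscopies counted in the urine arm. Both measures are needed, because withdrawal at recurrence and attrition make follow-up unequal and a proportion of participants alone ignores this.
- Present the arm table as a supplement to the complications model of section 3.2.4, not a replacement for it.

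The cost is reporting wording, slightly wider intervals and one extra table. Data collection and sample size do not change.

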### Stopping rules for evidence of harm

3.4

We will follow stopping rules if there is evidence that urine testing increases recurrence or progression.

For recurrence, we will calculate the cumulative incidence of recurrence for each arm when half of the total follow-up has accumulated. We anticipate that this analysis will happen approximately 1 yr after half of the participants have been enrolled. We will compare the cumulative incidence in the urine testing arms with that in the frequent cystoscopy arm using a log-rank test. If the cumulative incidence of recurrence is statistically significantly higher in one of the urine testing arms than in the frequent cystoscopy arm with an alpha level of 0.05, then the respective urine testing arm will be closed for enrollment and all the participants from that arm will be transitioned to the standard of care. Based on power calculations, this would require a hazard ratio of ≥3.2.

We will assume that progression to more dangerous disease was missed at an unacceptable rate by urine testing if four participants in a urine testing arm develop progression to muscle-invasive disease that is detected at the 12- or 24-mo cystoscopy visit, but was not detected with the preceding 6- or 18-mo respective urine tests. If four participants in the Xpert Bladder Cancer Monitor test arm fit this scenario, then the Xpert urine test arm will be closed for enrollment and all the participants from that arm will be transitioned to the standard of care. If four participants in the EpiCheck urine test arm fit this scenario, then the EpiCheck urine test arm will be closed for enrollment and all the participants from that arm will be transitioned to the standard of care.

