### Interventions

2.2

Comparators include programmatic surveillance using (1) the Xpert Bladder Cancer Monitor test, (2) the Bladder EpiCheck urine test, or (3) frequent cystoscopy. After a negative cystoscopy ≤4 mo following bladder tumor resection, all the participants will undergo surveillance visits at 6, 12, 18, and 24 mo—a surveillance schedule that is in line with the current guideline recommendations [1], [16]. In the urine testing arms, surveillance visits at 6 and 18 mo will include a visit with the clinician and urine testing with the respective urine test; in case of a positive test result, the participant will undergo an immediate cystoscopy. In the frequent cystoscopy arm, surveillance visits at 6 and 18 mo will include a visit with the clinician and cystoscopy. Regardless of the arm, participants will undergo surveillance visits that include a visit with the clinician and cystoscopy at 12 and 24 mo (see the study schema in Fig. 1). Note that time zero is defined as the date of the most recent bladder tumor resection.

The 12- and 24-mo cystoscopy procedures were included in the urine testing arms for safety reasons. During the planning of this study, both urologists and patients were concerned about “missing cancer.” These cystoscopy procedures will assure that the maximal delay in finding a recurrent cancer in the urine testing arms will be no more than 6 mo. A 6-mo delay is highly unlikely to affect long-term outcomes in this intermediate-risk bladder cancer population, as these patients have only a 1% risk of cancer progression within 1 yr [17].

At the treating clinician’s discretion, any patient is allowed to undergo a for-cause cystoscopy, for example, for gross hematuria or new voiding symptoms. This provides additional reassurance that any participant’s bladder can be inspected directly as per the treating clinician’s discretion if believed to be necessary due to symptoms. Thus, the option to perform for-cause cystoscopy procedures will further minimize the risk of delay in diagnosis of cancer recurrence. Additional bladder cancer clinical evaluations and treatment will also be at the discretion of the treating clinician, and all evaluations and treatments will be recorded.

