#### Surveillance report

2.6.2

The clinical research coordinator will collect the date of surveillance, type of surveillance performed (ie*,* urine testing or cystoscopy, or standard or enhanced cystoscopy), results of surveillance testing (negative, suspicious, or positive), and next step recommended by the provider. This will allow us to ascertain the type of surveillance that each participant underwent, which will serve as a fidelity measure.

We will also record any evaluations or treatments received since the last visit. This will include dates and results of any for-cause evaluations (eg, cystoscopy or upper tract imaging done for hematuria), and dates and pathology of any bladder biopsies or resections, of any intravesical treatments, and of other bladder cancer–directed therapy. These data will allow us to calculate the number of invasive procedures that each patient underwent during the study period (exploratory outcome).

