#### Bladder cancer recurrence/progression

2.6.4

Bladder cancer recurrence is defined as any bladder abnormality detected during study follow-up, which is biopsied or resected, with local pathology confirming urothelial carcinoma. Note that we require pathological confirmation of recurrence; thus, in-office fulguration without biopsy should not be performed.

Bladder cancer progression is defined as stage or grade progression according to the International Bladder Cancer Group [23], development of metastatic disease, or bladder cancer death. The clinical research coordinator will perform a chart review after each surveillance visit and at participant termination. For participants who developed a recurrence or progression, pathological details of this recurrence or progression will be abstracted from the chart. Following data collection, these participants will be withdrawn from the study and will undergo further treatment and surveillance as per the standard of care.

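### The four-participant progression stopping rule counts only muscle-invasive cancers found at the scheduled 12- or 24-month cystoscopy, so one found for cause after an undetecting marker cannot enter the count

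*Protocol article*

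**What the plan says.** Section 3.4 (Stopping rules for evidence of harm) has two rules. The one at issue is meant to show whether a marker misses dangerous progression too often. It is met "if four participants in a urine testing arm develop progression to muscle-invasive disease", and a case is defined as "progression to muscle-invasive disease that is detected at the 12- or 24-mo cystoscopy visit, but was not detected with the preceding" 6- or 18-month urine test. The consequence is then given arm by arm, for example: "If four participants in the Xpert Bladder Cancer Monitor test arm fit this scenario, then the Xpert urine test arm will be closed for enrollment". That arm's participants then return to standard care.

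Three other parts of the protocol bear on which cancers can become cases:

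- Section 2.2 (Interventions): "any patient is allowed to undergo a for-cause cystoscopy, for example, for gross hematuria or new voiding symptoms". The stated reason is that "the option to perform for-cause cystoscopy procedures will further minimize the risk of delay in diagnosis of cancer recurrence".
- Section 2.6.4 (Bladder cancer recurrence/progression): once the details of a recurrence or progression have been collected, "these participants will be withdrawn from the study".
- Section 2.6.2 (Surveillance report), on what is recorded at each visit about events since the last one: "This will include dates and results of any for-cause evaluations", together with the dates and pathology of biopsies and resections.

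**The concern.** The rule asks whether the marker missed an invasive cancer, but it defines a case by two conditions: the marker did not detect it, and a scheduled cystoscopy did. The second condition concerns how the cancer came to light. It says nothing about whether the marker missed it. A participant whose missed cancer causes bleeding before the scheduled visit is sent down the for-cause route, is withdrawn, and drops out of the count.

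This is the only rule in the protocol directed specifically at muscle-invasive disease. The for-cause route, offered as a safeguard for the individual participant, takes events away from the safeguard for the arm. No other sentence in the article extends the count to cancers found between visits.

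**Working it through.** **Applying the text to single cases in a urine testing arm**

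1. Marker negative at 6 months; muscle-invasive disease found at the 12-month cystoscopy. Both conditions are met, so it is counted.
2. Marker negative at 6 months; hematuria at, say, 9 months; for-cause cystoscopy shows muscle-invasive disease. The second condition fails, so it is not counted. Withdrawal under section 2.6.4 means there is no later 12-month study visit at which it could be.
3. The same sequence between the 18-month marker and the 24-month cystoscopy gives the same result.

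No sequence works in the other direction, adding a case that would not otherwise count. The error can only lower the count.

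**Size**

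The protocol gives no operating characteristics for the four-participant rule, so there is no figure to reproduce. The illustration uses:

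- n = 80 per arm (section 3.1) and a threshold of 4 (section 3.4);
- m, the probability per participant of a muscle-invasive cancer missed by the marker: *assumed*, 2%, 5% and 10%;
- q, the share of those cancers found for cause before the next scheduled cystoscopy: *assumed*, 0 to 75%.

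The counted number X is taken as binomial with n = 80 and probability π = m(1 − q), and

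P(X ≥ 4) = 1 − Σ(k = 0 to 3) C(80, k) π^k (1 − π)^(80 − k).

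Example with m = 5% and q = 50%: π = 0.025. The terms for k = 0, 1, 2, 3 are 0.132, 0.271, 0.274 and 0.183, which sum to 0.859, so P(X ≥ 4) = 0.141.

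| Missed rate m | q = 0 (all counted) | q = 25% | q = 50% | q = 75% |
|---|---|---|---|---|
| 2% | 0.077 | 0.033 | 0.009 | 0.001 |
| 5% | 0.57 | 0.35 | 0.14 | 0.02 |
| 10% | 0.96 | 0.86 | 0.57 | 0.14 |

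Put another way, four counted cases correspond in expectation to 4/(1 − q) true misses: 5.3, 8 and 16 at q = 25%, 50% and 75%.

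**Anchor**

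Section 2.2 puts the risk of progression at 1% within a year, not restricted to muscle-invasive disease. Carried over two years that is about 2%. The 2% row is therefore already the case in which all of that progression is muscle-invasive and the marker misses every one. The 5% and 10% rows are 2.5 and 5 times that total.

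**The case against.** The strongest reply concerns weight. Table 1 gives high-grade sensitivities of 0.88 and 0.91. If 2% progressed over two years, all of it invasive, and the marker missed 12%, the missed rate would be 2% × 12% = 0.24%. Four cases among 80 would then have a probability below 0.0001 under either definition. That stands: at the protocol's own expectations the rule almost never fires, however cases are counted. It does not remove the gap, because a harm rule exists for the case in which the expectations are wrong.

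The share q has no basis in the protocol, and at small q the loss is modest. That also stands, and it is why a range is shown. It is plausible that the more symptomatic missed cancers are the ones removed, but the protocol does not establish it.

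A reader might infer that these cancers vanish from the trial's safety data. They do not. For-cause results are recorded (section 2.6.2), chart review captures progression (section 2.6.4), and it is analysed as an exploratory outcome (section 3.2.4). A pathologically confirmed case also meets the definition of recurrence, so it enters the log-rank stopping comparison if found before that single interim look. None of these routes feeds the four-participant count, however, and the recurrence rule pools all recurrences and by the protocol's own figure needs a hazard ratio of at least 3.2.

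A reader might also infer that metastatic or fatal progression before the scheduled visit is wrongly left out. Section 3.4 chose muscle-invasive disease as its event. Adding metastasis or death would change the endpoint as well as the route of detection, and nothing in the protocol shows that choice to be an error.

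Finally, the sections do not contradict one another, since all can be followed at once. A fuller protocol might deal with interval cancers, but the article defines the counted event explicitly, and a wider definition elsewhere would depart from that text.

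**Conclusion.** The point holds for the four-participant rule and for muscle-invasive cancers found between an undetecting marker and the next scheduled cystoscopy. Followed literally, section 3.4 cannot count them, so the rule can only understate the misses it is meant to detect.

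The size depends on two quantities that the protocol does not give. If half of the misses surface early, the chance of reaching four falls from 0.077 to 0.009 at a 2% missed rate, from 0.57 to 0.14 at 5%, and from 0.96 to 0.57 at 10%. These figures treat all 80 participants as at risk; attrition and withdrawal for recurrence are ignored.

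Because the protocol expects only about 1% progression of any kind within a year, the gap matters mainly if that expectation fails. The documents do not support a conclusion that the trial lacks safety monitoring or that the threshold of four is wrong. The change is worth making because it corrects a stated safety rule at almost no cost.

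**What to change.** Reconcile section 3.4 with sections 2.2 and 2.6.4 so that a case is defined by the marker miss: muscle-invasive progression first diagnosed by any route after a 6- or 18-month marker that did not detect it, up to and including the next scheduled cystoscopy. Leave the threshold of four and the muscle-invasive endpoint unchanged. Whether metastatic or fatal progression should also count is for the sponsor to decide and state.

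The cost is one sentence and no new data, since section 2.6.2 already collects the dates, results and pathology needed. There are two downsides. The count may reach its threshold slightly more often. And some interval tumours may have arisen after the test and so not be true misses, although the same is true of tumours found at the scheduled visit.
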